### Control

Parents allocated to the wait-list control group will not receive the intervention until final follow-up is complete, that is, at the end of the 12-week study period. At this stage, participants will be offered the 3PS program, including the opportunity to participate in the workshop and access to the study website.

### Outcomes

Participants in the intervention group will be asked to complete their 6- and 12-week questionnaires 6 and 12 weeks after the date of the workshop they attend, respectively. Furthermore, 3 workshop dates will be offered on 3 consecutive Saturdays. Participants in the wait-list control group will complete their 6- and 12-week questionnaires 6 and 12 weeks from the date of the first workshop, respectively.

Table 1 illustrates the schedule of outcome assessments for both study groups. All measures will be taken at baseline, 6 weeks, and 12 weeks in both the intervention and control groups, unless stated otherwise. The baseline will contain sociodemographic questions focused on the child, including age, sex, and ethnicity, in addition to questions focused on the caregiver, including age, gender, ethnicity, marital status, employment status, household income, relationship with child, household size, and family structure.

**Table 1 table1:** Schedule of assessments.

Outcomes		Baseline	6 weeks	12 weeks
**Screen use (primary)**				
	Total screen time^a^ (minutes)	x^b^	x	x
	Percentage of children meeting screen recommendations^c^	x	x	x
**Sleep**				
	Brief Screening Questionnaire for Infant Sleep Problems-Extended [83]	x	x	x
**Family meals and nutrition**				
	Frequency of family meals [84]	x	x	x
	Fruit servings per day^a^	x	x	x
	Vegetables servings per day^a^	x	x	x
	Frequency of sugar-sweetened beverages in the previous week^a^	x	x	x
	Frequency of fast foods in the previous week^a^	x	x	x
	Feeding Practices and Structure Questionnaire [85]	x	x	x
**Daily routines and** **household**				
	Child Routine Inventory^d^ [86]	x	x	x
	Chaos, Hubbub, and Order Scale [87]	x	x	x
**Program feedback^e^**				
	Exit questionnaire	—^f^	—	x
	Exit interview	—	—	x

^a^New Zealand Health Survey Questions.

^b^x: measure taken.

^c^Less than 1 hour per day.

^d^Daily Living Routines subscale only.

^e^Intervention group only.

^f^Not applicable.

#### Primary Outcomes

The primary outcome is screen time at 6 weeks, which is one of the program’s targeted routines and the primary endpoint used in a previous study [15]. Furthermore, although increasing screen-free play and, in turn, reducing screen use is one of the targeted routines of the 3PS program, reducing screen use is also promoted as a way to increase connection during family meals and bedtime. For example, parents are advised to turn off screens during family meals and to avoid screen use during the bedtime routine. Given that screen use is either targeted directly or indirectly in each of the 3 routines included in the 3PS program, the decision was made to include it as the primary endpoint for the study.

Screen time will be assessed using 4 questions from the New Zealand Health Survey [88], which were developed by the New Zealand Ministry of Health to measure the amount of time New Zealand children aged 2 to 14 years spend using screens recreationally. Parents report the time (in hours) that their child spends watching television or using *other* screen devices, including mobile phone, tablets, video game consoles, and computers, during weekdays and on weekends. Screen time will be measured as both a continuous variable, that is a decrease from baseline in average screen time, and a binary variable, that is the proportion of children meeting the screen time recommendations of less than 1 hour per day.

#### Secondary Outcomes

Family meals, diet, and parent feeding practices: A single item investigating the frequency of family meals, taken from the validated Family Routines Inventory questionnaire [84] and used in the 45-month *Growing Up in New Zealand* data collection wave, will assess participation in family meals. Moreover, 4 questions from the New Zealand Health Survey will investigate the number of fruit and vegetable servings, fizzy drink consumption, and fast-food consumption. A modified version of the Feeding Practices and Structure Questionnaire [85], which includes 17 questions investigating 4 domains of parental feeding behaviors, will also be administered: (1) reward for behavior, (2) reward for eating, (3) persuasive feeding, and (4) structured meal setting.

Sleep: Sleep will be assessed using the Brief Screening Questionnaire for Infant Sleep Problems-Extended [83] -Adapted. The questionnaire asks parents to report outcomes investigating their child’s nocturnal sleep duration, night waking, method of falling asleep, sleeping arrangements, bedtime rituals, and parental interventions. The Web-based version of the questionnaire has been validated for toddler sleep in a New Zealand and Australian sample [89].

Routines and Home Environment: The *Daily Living Routines* subscale of the Child Routine Inventory [86] will investigate engagement in standard routines of daily life. The subscale involves 11 parent-reported questions. Scores will be summed with higher scores indicating greater frequency of routines. The 15-item Chaos, Hubbub, and Order Scale [87] investigates the level of chaos in the home. A total score will be derived by obtaining a sum of responses for the 15 items, where higher scores represent a more chaotic, disorganized, and hurried home environment.

Exit Questionnaire: The exit questionnaire, completed at 6 weeks by intervention participants only, will assess acceptability and feedback of the 3PS program using 5 open-ended questions about what the participants liked and disliked about the program and what they would keep the same or change.

Exit Interviews: A subgroup of 6 to 10 intervention participants will take part in an exit interview at the 6-week follow-up. The exit interview will be conducted by a trained research assistant on the telephone or face-to-face at a community venue and will take approximately 20 min. Participants will be asked to provide informed consent before participating in the interview. Participants will be prompted to explore in more depth their responses to the exit questionnaire, in particular, whether they used the study website and if they found it helpful. Furthermore, given that the formative work revealed that many parents had concerns about parenting interventions making them feel guilty and judged, we will explore their perceptions of the language and tone used in the program and explore ways in which we could avoid any negative experiences in the future.

### Sample Size

We will aim to recruit 50 people (25 in each group). As this is a pilot trial, it is not powered to detect significant differences between the 2 groups but will provide sufficient data to ascertain recruitment and the direction and likely effect size for the screen-time outcomes.

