**Conclusions:**

Findings from this pilot study will provide relevant data to inform the design of a larger effectiveness study of the 3PS program.

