### Randomization

The research assistant will use sequentially numbered, opaque, sealed envelopes to randomize participants. Participants will be allocated to 1 of the 2 groups in a 1:1 ratio using block randomization with varying block sizes of 2 and 4. The randomization sequence will be generated by the study statistician, who will also prepare and seal the envelopes.

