### Reporting of Results

#### Statistical Analysis

Study data will be collected in REDCap. All statistical analyses will be performed using SAS version 9.4 and will be specified a priori in a statistical analysis plan prepared by the study statistician. All baseline variables will be summarized by group and descriptive summary statistics provided. Analyses will be carried out on an intention-to-treat basis. Chi-square tests, incidence rates, relative risks, and 95% CI will be calculated for all binary variables followed by multiple logistic regression analysis adjusting for other variables if needed. Continuous data will be analyzed using multiple linear regression modeling or nonparametric analysis. Sensitivity analyses will be undertaken to determine the impact of missing data. Repeated measures models will be used to analyze data collected repeatedly over time. A trained research assistant will conduct interviews. Interviews will be recorded (with permission) and transcribed verbatim. A general inductive thematic approach will be followed that allows research findings to emerge from multiple readings of the raw data. NVivo9 software will be used to manage the transcripts and facilitate the analysis process and to identify themes and categories.

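### With 25 per arm the pilot cannot, as the Sample Size section claims, ascertain the direction and likely size of a small to moderate effect on screen time

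*Protocol article*

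**What the plan says.** The Sample Size section of the protocol article aims for 50 participants, 25 in each group. It says that, as a pilot, "it is not powered to detect significant differences between the 2 groups", but that it "will provide sufficient data to ascertain recruitment and the direction and likely effect size for the screen-time outcomes". No SD, target effect, confidence level or interval width is offered in support.

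Under Primary Outcomes, "The primary outcome is screen time at 6 weeks". The same section adds: "Screen time will be measured as both a continuous variable, that is a decrease from baseline in average screen time, and a binary variable", the binary form being the share of children within the one-hour daily recommendation. The claim therefore covers a continuous and a binary outcome.

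The Abstract gives the intended use: "Findings from this pilot study will provide relevant data to inform the design of a larger effectiveness study". The Discussion repeats it.

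**The concern.** One sentence disclaims power and then claims something close to it. To ascertain direction at 95% confidence is to have a 95% interval that excludes zero. That is the two-sided 5% test for which the sentence says the trial lacks power. To ascertain a likely effect size asks for more: an interval narrow enough to tell a negligible effect from a worthwhile one.

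The stake is the next trial. A reader who takes the sentence at its word could carry the pilot's point estimate into the sample size of the larger study, or read its sign as a verdict on the program. If the estimate is mostly noise, either step goes astray.

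**Working it through.** **Inputs from the protocol article.** 25 per arm (Sample Size); 1:1 allocation (Randomization); screen time as a continuous and a binary outcome (Primary Outcomes); 95% confidence intervals (Statistical Analysis, which names them for binary variables).

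**Assumptions, because the article gives no figure.** True standardised difference d from 0.2 to 0.8; two-sided 5% level; loss of 0% or 20% (25 or 20 per arm analysed); baseline to follow-up correlation r of 0.5 or 0.7; 10% or 20% of controls and 20% or 40% of the intervention group meeting the recommendation. Differences are in units of the between-child SD of screen time at follow-up.

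The article shows no calculation behind 50, so there is no figure to reproduce. The check is on the sufficiency claim.

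**1. Interval width, continuous outcome.** SE = √(2/n); half-width = t(0.975, 2n−2) × SE.
- n = 25: SE = √(2/25) = 0.283; half-width = 2.011 × 0.283 = 0.57 SD.
- n = 20: SE = √(2/20) = 0.316; half-width = 2.024 × 0.316 = 0.64 SD.
- n = 25, baseline-adjusted, SE multiplied by √(1−r²): 0.49 SD at r = 0.5 and 0.41 SD at r = 0.7.
- n = 25, simple change from baseline, SE multiplied by √(2(1−r)): 0.57 × 1.00 = 0.57 SD at r = 0.5 and 0.57 × 0.775 = 0.44 SD at r = 0.7.

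These widths do not depend on the true effect. Unadjusted at 25 per arm, an observed 0.3 has the interval 0.3 ± 0.57 = −0.27 to 0.87, and an observed 0.5 has −0.07 to 1.07.

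**2. Chance that the point estimate has the wrong sign.** Φ(−d/SE); for d = 0.2 and n = 25, Φ(−0.2/0.283) = Φ(−0.71) = 0.24.

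| True d | 25 per arm | 20 per arm | 25 per arm, baseline-adjusted (r = 0.5 / 0.7) |
|---|---|---|---|
| 0.2 | 24% | 26% | 21% / 16% |
| 0.3 | 14% | 17% | 11% / 7% |
| 0.5 | 4% | 6% | 2% / 1% |

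**3. Chance that the interval excludes zero on the right side.** This is the power of the two-sided 5% test. Unadjusted at 25 per arm it is about 11%, 18%, 42% and 81% for d = 0.2, 0.3, 0.5 and 0.8 (normal approximation).

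**4. Binary outcome, 25 per arm.** SE of log RR = √[(1−p₁)/(n·p₁) + (1−p₂)/(n·p₂)].
- 20% v 40%: √(0.8/5 + 0.6/10) = √0.22 = 0.469. RR = 2.0, 95% CI 2.0 × exp(±1.96 × 0.469) = 0.80 to 5.0. The observed proportions are reversed or tied 8% of the time.
- 10% v 20%: √(0.9/2.5 + 0.8/5) = √0.52 = 0.721. RR = 2.0, 95% CI 0.49 to 8.2. Reversed or tied 21% of the time.

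**5. What sizing on the pilot effect would mean.** n per arm = 2(1.96 + 0.842)²/d² = 15.70/d², for 80% power. An observed 0.3 gives 15.70/0.09, so 175 per arm. Values inside its own interval give 21 (d = 0.87) and 1,570 (d = 0.1), with no finite size at zero or below.

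**6. What the pilot can do.** At an assumed 80% retention among 50 randomised, the 95% half-width is 1.96 × √(0.8 × 0.2/50) = 11 percentage points; at 90% it is 8. Those are usable planning figures.

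**The case against.** The best defence is that the section says openly that the pilot is not powered, and that the direction of a point estimate is a looser notion than a significant result. On that reading the claim is nearly true for a large effect: the unadjusted estimate has the right sign about 96% of the time at 0.5 SD and 99.8% at 0.8 SD. Baseline adjustment is also plausible, since the outcome is framed as a decrease from baseline and the analysis uses regression. Both points stand, and they are why the criticism is confined to small to moderate effects and why ±0.57 SD must be labelled unadjusted with full retention. They do not rescue the sentence. The article gives no reason to expect a large effect, and even the adjusted ±0.41 SD leaves the size of effect open.

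Four stronger readings may tempt a reader, and the article does not support them.
- *The planned tests contradict the disclaimer.* Lack of power limits how a test is read; it does not forbid testing. The only test named is in "Chi-square tests, incidence rates, relative risks, and 95% CI will be calculated for all binary variables", which already pairs it with estimates and intervals.
- *Recruitment cannot be ascertained because it is not a listed outcome.* Recruitment counts arise from the enrolment process the article describes, and a condensed article need not tabulate them.
- *The sign of no small or moderate effect can be established.* That is too absolute, given the figures at 0.5 SD.
- *The larger trial will be sized on the pilot estimate.* The article says only that findings will inform its design, which is equally true of SD, recruitment and retention. The risk comes from presenting the effect size as ascertainable.

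**Conclusion.** The claim about direction and likely effect size is wrong as written for small to moderate effects. The half-width is 0.57 SD in the unadjusted full-retention case, and 0.41 to 0.64 SD across the retention and adjustment cases shown in step 1. The wrong-sign risk is 16% to 26% at a true 0.2 SD, 7% to 17% at 0.3 and 1% to 6% at 0.5. The binary outcome is as imprecise under the assumed rates.

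The unadjusted half-width at 25 per arm rests only on the stated group size, equal allocation and a 95% level. Every figure that depends on a true effect, correlation, loss or event rate rests on an assumption, since the article gives none. The part of the sentence about recruitment is unaffected, and so are the planned tests. The sample size itself is not at fault: 25 per arm is defensible for a pilot that does not claim to settle the effect.

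**What to change.** Replace the sentence in Sample Size with wording to this effect:

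> The pilot will estimate recruitment, retention and the SD of screen time, and will report the between-group difference in screen time with its 95% confidence interval (half-width about 0.57 SD unadjusted with full retention, narrower with baseline adjustment). It is not intended to ascertain the direction or size of the effect. The size of the larger trial will be based on a minimally important difference, with the SD and retention seen in the pilot, and not on the pilot's point estimate.

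Report the relative risk for the binary outcome in the same spirit, with its interval given equal prominence. The planned tests can stay, and no outcome need be added.

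The cost is wording, plus agreeing a minimally important difference before the larger trial is planned. The article reports that follow-up is complete, so no change of design is involved: what changes is how the results are read and used. The downside is that a stated claim for the pilot becomes less favourable.

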### Reporting of Results

#### Statistical Analysis

Study data will be collected in REDCap. All statistical analyses will be performed using SAS version 9.4 and will be specified a priori in a statistical analysis plan prepared by the study statistician. All baseline variables will be summarized by group and descriptive summary statistics provided. Analyses will be carried out on an intention-to-treat basis. Chi-square tests, incidence rates, relative risks, and 95% CI will be calculated for all binary variables followed by multiple logistic regression analysis adjusting for other variables if needed. Continuous data will be analyzed using multiple linear regression modeling or nonparametric analysis. Sensitivity analyses will be undertaken to determine the impact of missing data. Repeated measures models will be used to analyze data collected repeatedly over time. A trained research assistant will conduct interviews. Interviews will be recorded (with permission) and transcribed verbatim. A general inductive thematic approach will be followed that allows research findings to emerge from multiple readings of the raw data. NVivo9 software will be used to manage the transcripts and facilitate the analysis process and to identify themes and categories.

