The second part of the workshop is more practical and divided into 3 sections that correspond with the 3 study pillars—supporting sleep, screen-free play, and family meals. Each of the pillars is introduced using a similar format; there is a background reading, which provides a brief overview as to why the activity is important to health and child development, and then the workshop facilitator walks the parents through the 5-step process outlined above as it relates to each specific pillar. For each of the 3 pillars, a number of group activities are used to encourage parent engagement and highlight the study messages and learnings. At the end of the workshop, parents will be given a study pack [15], which includes a meal planner and candle, to promote creating a routine around family meals (eg, lighting a candle at the start of each meal); a child’s book, to encourage reading during the bedtime routine; and a sketch pad and crayons, to encourage free play.

Due to the intensive nature of the workshop, parents will also be given access to a study website. This website will allow parents to return to the material covered during the 3PS workshop and review it at their own pace. In addition to providing all the content delivered during the workshop, the website will also include links to related readings, selected references (as a number of parents said they wanted to know the *science* behind the approach), and extra tips around common feeding and sleep issues in preschoolers. Parents will be sent a link to the study website after the workshop.

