Participants log-in to the 3PS website on the study landing page and then are taken to a homepage, which has links to 4 additional pages: (1) the CARE Framework page, which discusses the framework used in detail; (2) the 3 Pillars page, which links to 3 subpages that reflect each of the pillars; (3) an Info page, which provides study-related information; and (4) a Contact Us page, which provides the contact information for the study team. For each of the 3 Pillars subpages, background is provided about how the specific pillar is related to child health and well-being, and a step-by-step approach to using the CARE Framework to address the pillar. For example, with respect to sleep, there is information about what children find disconnecting at bedtime, what a simple bedtime routine might look like, a list of ideas for how parents might be able to infuse connection into the bedtime routine, and then ideas for reducing household chaos to create a peaceful sleep environment. Their access to the study website will be active for a period of 6 weeks.

Participants will be given the choice of attending 1 of the 3 half-day workshops. The day before the workshop, participants will be contacted via email with a reminder of the workshop and also detailed instructions of where to find the room and parking. If a participant does not turn up to the workshop, they will be contacted via phone or email to reschedule the workshop they attend, in an attempt to improve study adherence. The workshop will be catered and dietary requirements provided for.

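### The program is delivered in three group workshops in one arm only, and no named analysis accounts for workshop; if the workshop ICC is above 0, the intervals for the program effect will be too narrow.

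*Protocol article*

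**What the plan says.** All places are in the protocol article.

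- **Randomization:** allocation is by individual: "Participants will be allocated to 1 of the 2 groups in a 1:1 ratio using block randomization".
- **Intervention:** "Participants will be given the choice of attending 1 of the 3 half-day workshops", and within each part of the workshop "a number of group activities are used to encourage parent engagement". Website access for 6 weeks follows. Parents who miss their session are contacted to rebook.
- **Outcomes:** "3 workshop dates will be offered on 3 consecutive Saturdays". Follow-up of intervention parents is timed from the workshop that they attend, and that of controls from the first workshop.
- **Control:** wait-list parents are offered the program only after the 12-week follow-up.
- **Statistical Analysis:** "Continuous data will be analyzed using multiple linear regression modeling or nonparametric analysis". Binary variables get chi-square tests, relative risks with 95% CIs and, if needed, logistic regression. Repeated measures models are named for data collected over time. Analysis is by intention to treat, and details are assigned to a separate statistical analysis plan, which is not shown.
- **Sample Size:** there are 25 parents per arm; "it is not powered to detect significant differences between the 2 groups", and the data are meant to show "the direction and likely effect size for the screen-time outcomes".

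**The concern.** This is an individually randomized trial with clustering in one arm (a partially nested design). Parents in the same workshop share the session, its group dynamics and, because follow-up is timed from the workshop, the calendar window in which they are measured. Controls share none of this.

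Chi-square tests, relative risks with ordinary CIs, rank tests and ordinary regression take each parent as an independent observation. Adding workshop as an ordinary covariate does not repair this. Controls have no workshop, so the three workshop indicators sum to the treatment indicator and are aliased with it.

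At stake is the stated precision of the screen-time effect, which is what the pilot is meant to pass on to the larger study. A positive workshop ICC makes the naive interval too narrow, never too wide.

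**Working it through.** **Figures in the plan.** There is none to reproduce. The target of 50 has no alpha, power, effect size or SD behind it, and no ICC is given.

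**Inputs from the article:** 25 parents per arm; 3 workshops; average workshop size 25/3 = 8.3.

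**Assumed:** workshop ICC ρ of 0.02, 0.05 and 0.10; workshop sizes 9, 8 and 8 (near-equal), or 15, 7 and 3 (uneven, since parents choose their date); full attendance and no dropout; equal total variance in the two arms.

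**Step 1, effective workshop size.** m = Σ(size²)/25.
- 9/8/8: (81 + 64 + 64)/25 = 8.36.
- 15/7/3: (225 + 49 + 9)/25 = 11.32.

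**Step 2, design effect in the intervention arm.** DE = 1 + (m − 1)ρ. For 9/8/8 at ρ = 0.05: 1 + 7.36 × 0.05 = 1.368.

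**Step 3, true SE over naive SE.** The naive variance of the difference is 2/25 and the true variance is (DE + 1)/25, in SD² units. The ratio of SEs is √((DE + 1)/2). At DE = 1.368: √1.184 = 1.088.

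**Step 4, coverage of the nominal 95% interval,** by normal approximation: 2Φ(1.96/ratio) − 1.

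| Sizes | ρ | DE | SE ratio | Coverage |
|---|---|---|---|---|
| 9/8/8 | 0 | 1.000 | 1.00 | 95.0% |
| 9/8/8 | 0.02 | 1.147 | 1.04 | 94.1% |
| 9/8/8 | 0.05 | 1.368 | 1.09 | 92.8% |
| 9/8/8 | 0.10 | 1.736 | 1.17 | 90.6% |
| 15/7/3 | 0.02 | 1.206 | 1.05 | 93.8% |
| 15/7/3 | 0.05 | 1.516 | 1.12 | 91.9% |
| 15/7/3 | 0.10 | 2.032 | 1.23 | 88.9% |

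A simulation of the pooled t interval with sizes 9/8/8 (100,000 trials per ICC) gave coverage of 95.0%, 92.9% and 90.6% at ρ = 0, 0.05 and 0.10, which agrees.

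**Step 5, width.** The naive half-width is t(48 df) × √(2/25) = 2.011 × 0.283 = 0.569 SD. Multiplied by 1.036, 1.088 and 1.170, it becomes 0.59, 0.62 and 0.67 SD at the three ICCs (9/8/8).

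**Step 6, could the workshop variance be estimated instead?** Three workshops leave 2 between-workshop degrees of freedom. For 9/8/8:
- The Satterthwaite df for the treatment difference are 6.6, 5.7 and 4.8 at ρ = 0.02, 0.05 and 0.10, and the interval is 1.23, 1.34 and 1.51 times as wide as the naive one. It is already 1.16 times as wide at ρ = 0, purely from estimating a variance on so few df.
- The chance that the between-workshop mean square falls below the residual mean square, so that the variance estimate is cut off at zero, is P(F(2, 22) < 1/(1 + 8.32ρ/(1 − ρ))), where 8.32 = (25 − 8.36)/2. This is about 56%, 49% and 40% at the three ICCs.

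A fitted model would therefore collapse to the unadjusted analysis in roughly half of such trials, and otherwise widen the interval sharply.

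**The case against.** The strongest reply is that this is a condensed article, that details of the models belong to an analysis plan not shown, and that linear, logistic and repeated measures models can all carry a workshop term. Part of this stands. A reader might infer that the plan asserts independence, or that its repeated measures models exclude workshop. The article says neither. But the chi-square tests, the relative risks with CIs and the nonparametric option are stated commitments, and in standard form they have no place for workshop. For these the mismatch with the design lies in what is written, not only in what is left out.

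A reader might also infer that the intervals certainly are too narrow. That needs an ICC above 0, which the article does not supply. After one half-day session and individual website use, the ICC may be small. The article describes a single facilitator, so a stable facilitator effect is common to all three workshops and adds no variance between them.

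A third tempting reading is that the larger trial would inherit a variance that omits the workshop component. This is largely wrong. The intervention-arm SD is taken across all workshops: E(s²) = σ²(1 − (7.36/24)ρ) = σ²(1 − 0.307ρ), a shortfall of 1.5% at ρ = 0.05 and 3.1% at ρ = 0.10 in that arm, and half as much when pooled. What the larger trial would lack is a usable ICC, and three workshops cannot supply one under any model.

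Finally, the pilot is not powered for a group comparison, so no confirmatory test or sample size is invalidated, and clustering does not by itself bias the point estimate. This stands, and it limits the consequence to precision.

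**Conclusion.** The point holds conditionally. Group delivery in one arm is documented, and the named analyses do not account for it. If the workshop ICC is above 0, the intervals for the program effect are too narrow: the true SE is about 4%, 9% and 17% above the naive SE at assumed ICCs of 0.02, 0.05 and 0.10 with near-equal workshops (5%, 12% and 23% with sizes 15/7/3). At an ICC of 0 the naive interval is right.

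These sizes rest on assumed ICCs, assumed workshop sizes and equal variance in the arms. The consequence is moderate: overstated precision for the effect size carried into the larger study.

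**What to change.** Keep the planned analysis and add the following.

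1. For screen time at 6 weeks, continuous and binary, report the treatment CI with the intervention-arm variance multiplied by DE = 1 + (m − 1)ρ at fixed ρ of 0.02, 0.05 and 0.10. Use the observed workshop sizes. Treat controls, and any intervention parents who attended no workshop, as singletons. With k such parents among n analysed in that arm, m = (Σ size² + k)/n, which keeps the intention-to-treat set intact. For the relative risk, apply DE to the intervention-arm term of the variance of the log relative risk.
2. State that the ICCs are assumed, and that the unadjusted CI is a lower bound on uncertainty if clustering exists.
3. Say that workshop clustering will be allowed for when the larger trial is sized, with an ICC range and not a pilot estimate.
4. A fitted partially nested model (random workshop effect in the intervention arm only) is optional and secondary, because three workshops cannot estimate the workshop variance.

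The cost is one table and somewhat wider intervals (half-width 0.59 to 0.67 SD against 0.57, near-equal workshops). It needs workshop attendance by participant but no new outcome data, so it remains possible although the article reports follow-up as complete.
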